#### Weight Watchers’ WW app

Those randomized to the Weight Watchers group will be given a unique link to download an app that includes information, resources, and food diary functions for the Weight Watchers diet. They will also receive a unique email and password, provided by the study team, to log in. The research team will pay for the WW app subscription, so there is no cost for participants randomized to the Weight Watchers group. Participants will be guided through connecting the iHealth scale and the WW app and given a brief overview of its features, with the remainder of the intervention will be delivered entirely via the app. Users will get information as to what to eat and what not to eat according to the Weight Watchers diet and points system [21].

The WW app takes a science-backed approach to weight loss that does not involve counting calories or macronutrients. Rather, all foods are assigned a point value. Certain foods are assigned a low number (eg, foods low in calories and fat, like lentils) and others are assigned a high number (eg, foods high in calories and fat, such as pizza). At the start of the program, participants will enter their current and goal weight for the next 12 weeks and complete a baseline assessment to determine current eating habits. Based on this information, participants will be assigned to one of 3 groups within the WW app (green, blue, or purple). Group assignment will determine the number of points allotted for the participant to eat in a day, as well as the number of weekly flex points that can be used if a participant goes over their allotted daily points. The app also contains approximately 100 to 300 zero-point foods (depending on the Weight Watchers group). These are low-calorie foods that participants can eat as much of and do not take any points away from daily or weekly allotted points. Participants record their dietary intake through the app, and the app automatically tracks their point intake and provides feedback to help users stay within their allotted point limit.

The WW app has similar support features as those of Keyto, such as live 24/7 dietary coaching and weight loss groups that participants can join for social support. Additionally, both apps offer recipes and meal plans to improve user experience and aid in dietary adherence. Both apps offer a food search option to allow users to determine if any food fits well into their eating plan.

### Measures

Participants will be asked to respond to survey measures at the 4 outcome time points: baseline and at 12, 24, and 48 weeks from start of the program. Daily and weekly questionnaires and app data will be used as manipulation checks of adherence and intervention fidelity, which are described below.

#### Outcome Measures

##### Body Mass

Participants will be asked to weigh themselves each morning using the Bluetooth weight scale (iHealth Lina H2). Weight measurements will be automatically uploaded to the iHealth cloud that can be accessed by the research team. Body mass measured at baseline, the initial measurement made at the start of the study, and follow-up time points (12, 24, and 48 weeks) will be calculated as the mean of measures taken across the week. A measure of daily adherence to self-weighing will also be examined as the total proportion of days that a participant records their weight.

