**Methods:**

A total of 144 participants will be recruited and randomized to either the Keyto program or Weight Watchers program. Study participants will be guided through the study via video conference or phone calls and will undergo a fasting blood analysis performed by a third-party diagnostic lab at weeks 0 and 12 to assess metabolic and cardiovascular risk markers. All participants will be asked to weigh themselves daily on a study-provided Bluetooth-enabled scale. Participants randomized to the Keyto arm will also be asked to measure their breath acetone levels, a measure of ketosis, with the Keyto device 3 times per day.

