**Primary outcome**				
	Bodyweight scale	Change in body mass (in kilograms)	12 weeks	Those in the Keyto intervention arm will achieve greater weight loss at 12 weeks than those in the Weight Watchers arm.

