### Recruitment, Screening, Randomization, Enrollment

Participants will be recruited through Facebook advertisements, poster advertisements placed in public spaces (eg, universities, libraries, coffee shops), and emails to the existing Keyto email list. Informed consent will be obtained digitally via Qualtrics (Qualtrics LLC). Following informed consent, participants will schedule a video conference or phone call with a member of the study team who will answer any questions participants may have, clarify the procedures of the study, and schedule a baseline blood test. After collection of the baseline blood sample, participants will be emailed the online baseline questionnaire. Participants will then be randomized by a researcher logging into a password-protected study website and mailed the study materials for their condition. All 144 participants will be randomized at 1:1 ratio to the Keyto (n=72) or Weight Watchers (n=72) trial arms using a variable permuted block sizes, stratifying for sex (male, female) and age (18-40 years, 41-64 years). The randomization website and schedule will be created and maintained by a third party (Centre for Health Evaluation and Outcomes Science, St. Paul’s Hospital, Vancouver, Canada). Participants will be provided with a US $100 gift card to an online store of their choice upon completion of the 48-week follow-up surveys.

**Table 2 table2:** Trial inclusion and exclusion criteria.

Criteria		

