### Interventions

#### Keyto App and Device

Those randomized to the Keyto arm will be asked to download the Keyto app from an app store. They will receive a unique email username and password provided by the study team to log in. Participants will be guided through connecting their iHealth scale and the Keyto app and given a brief overview of its features, with the remainder of the intervention will be delivered entirely via the app. The app contains resource information about what to eat and what not to eat in order to achieve nutritional ketosis and ample resources. The app also contains a social support function. For the trial, all Keyto participants will be placed into a moderated support group of 4 to 6 participants per group. Keyto’s registered dietician and executive medical director will be added to each group to answer questions about Keyto and starting a ketogenic diet. The identities of each user will be kept anonymous and users will be encouraged to refrain from using their names in this forum. Based on the premium version of the Keyto app, a phone or video conference call with the registered dietician will be available in the second week of the program. The app also includes tips and resources about how to succeed potential side effects or pitfalls. There is access to a short podcast offered 3 times per week discussing various aspects of the program including strategies and pitfalls.

The Keyto app uses its Key Eats nutrition plan as a heart-healthy ketogenic diet that emphasizes fish and plant-based fats, moderate protein and nonstarchy vegetables and is compatible with a vegetarian or mixed-diet lifestyle. The app reinforces users to avoid foods with refined carbohydrates like pasta, bread, pizza, or sweets and replacing those with foods high in healthy fats such as avocados, nuts, fatty fish (such as salmon), and olive oil.

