### Potential Risks and Mitigation

The potential risks of this research are minimal and relate to following a low-carbohydrate diet. As with many dietary changes, the switch to a low-carbohydrate diet can sometimes lead to headaches, nausea, or low energy. The Keyto program uses a modified ketogenic or low-carbohydrate high-fat diet which derives 70% of calories from fat. At the beginning of low-carbohydrate high-fat diets, some participants may experience transient adverse side effects including headache, light-headedness, achiness, and muscle cramps [34]. These side effects are sometimes referred to as the “keto flu [35],” appear to be related to changes in electrolytes and diuresis and can be mitigated by broth or bouillon supplementation and adequate sodium intake. The intensity of these symptoms is expected to decline as the study progresses and participants become adapted to a ketogenic diet. Possible long-term adverse side effects of ketogenic diets in adults who are overweight and obese, but otherwise healthy, are currently unknown.

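### Baseline body mass for the primary endpoint is defined in two ways and is not tied to the time before the diet, so early loss may be averaged into it

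*Protocol article*

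**What the plan says.** Table 1 makes change in body mass at 12 weeks the primary outcome, with the hypothesis "Those in the Keyto intervention arm will achieve greater weight loss at 12 weeks than those in the Weight Watchers arm".

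The Body Mass section defines the measurement in one sentence. Its subject is "Body mass measured at baseline, the initial measurement made at the start of the study, and follow-up time points" (12, 24 and 48 weeks), and its verb phrase is "will be calculated as the mean of measures taken across the week". Which week is meant is not stated. The Measures section counts the survey time points from the start of the program.

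The section on recruitment, screening, randomisation and enrolment sets the order: consent, call, baseline blood sample, baseline questionnaire, then "Participants will then be randomized by a researcher logging into a password-protected study website and mailed the study materials for their condition". No other mailing is described.

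According to the abstract, participants will "weigh themselves daily on a study-provided Bluetooth-enabled scale". The two intervention sections bring the scale in alongside the allocated app: "Participants will be guided through connecting their iHealth scale and the Keyto app" and "Participants will be guided through connecting the iHealth scale and the WW app".

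Potential Risks and Mitigation says that early side effects of low-carbohydrate, high-fat diets "appear to be related to changes in electrolytes and diuresis".

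**The concern.** Grammatically, the weekly mean covers baseline as well as the follow-ups, yet the same sentence describes baseline as one first reading. These are different quantities. Two analysts who both follow the text could produce different primary results, and in an open-label trial that choice could be made after the data are seen.

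The baseline blood sample and questionnaire come before allocation in the article's sequence. For weight, no step before allocation is described. If the scale arrives with the other materials and the baseline week is the first week of use, baseline is measured after allocation is known and while the diet is already acting. A baseline affected by treatment takes part of the effect out of the change from baseline. Baseline adjustment does not cure this, and neither does a mixed model of group differences over time. The same baseline also feeds the 24- and 48-week comparisons.

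Only the difference between arms in first-week loss matters, because a loss common to both arms cancels. The article's remark on diuresis gives a reason to expect a faster early fall in the Keyto arm, which would pull the contrast toward zero.

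**Working it through.** **Inputs from the Sample Size Calculation section:** target difference 5% of 100 kg = 5 kg; SD 15 kg; correlation r = 0.75; alpha 0.05 (taken as two-sided); power 80%; total 124 before loss to follow-up.

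**Step 1. Reproduce the stated size.** The baseline-adjusted SD is 15 × √(1 − 0.75²) = 9.92 kg. Then n per arm = 2 × [(1.960 + 0.842) × 9.92 / 5]² = 61.8, rounded up to 62, so 124 in total. This matches the plan. For a change score the SD is 15 × √(2 × (1 − 0.75)) = 10.61 kg, which needs 71 per arm, or 142. The article does not say that 124 was obtained by the first route. The formula only supplies a reference point.

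**Step 2. How much early loss enters a 7-day mean.** The documents give no week-1 weights, so let D be the extra Keyto loss by day 7, assumed to build up linearly. Averaging seven daily weighings captures
- days 0 to 6: (0 + 1 + … + 6) / 49 = 0.43 of D;
- days 1 to 7: (1 + 2 + … + 7) / 49 = 0.57 of D.

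**Step 3. What is removed from the 5 kg.** A change score loses the whole baseline contrast, b = 0.43D to 0.57D. A baseline-adjusted analysis with slope 0.75 loses 0.75 × b. Power uses the normal approximation with 62 per arm.

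| Assumed D (kg) | Change score: effect left (kg) | Power | Baseline-adjusted: effect left (kg) | Power |
|---|---|---|---|---|
| 0 | 5.00 | 75% | 5.00 | 80% |
| 0.5 | 4.79 to 4.71 | 71 to 70% | 4.84 to 4.79 | about 77% |
| 1 | 4.57 to 4.43 | 67 to 64% | 4.68 to 4.57 | 75 to 73% |
| 2 | 4.14 to 3.86 | 59 to 53% | 4.36 to 4.14 | 69 to 64% |

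For D from 0.5 to 2 kg, the change score loses 0.21 to 1.14 kg, and 0.21/5 to 1.14/5 is 4 to 23%. The adjusted analysis loses 0.16 to 0.86 kg, or 3 to 17%.

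The 75% in the first row is not caused by the baseline problem. It is what 62 per arm gives with the change-score SD.

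**Step 4. The other reading.** If baseline is a reading taken before the diet starts, b = 0 and nothing is lost, even if the reading comes after randomisation.

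**The case against.** The strongest reply is that the sentence itself calls baseline the initial measurement, so the weekly mean may be meant for the follow-ups only. Weighing takes place each morning, so a first-day reading would come before that day's eating. Even if baseline is averaged, the week could precede the diet. This is fair, and it makes the bias conditional. It does not remove the defect, because the wording supports both readings and fixes neither.

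A reader might go further and infer three things that the documents do not support.

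- *That the scale is mailed after randomisation.* The article does not say so. It mentions materials for the assigned condition, and the scale is common to both arms. Late delivery is the natural inference because no other mailing and no earlier study weighing is described. A weighing after allocation but before the diet would not cause this bias.
- *That early loss is in fact subtracted from the effect.* This holds only if the averaging week falls within the diet and the arms differ in that week. The diuresis remark concerns side effects and gives no weights.
- *That early withdrawals have no weight at all.* This applies only to people who leave before a first scale reading. A mixed model can use anyone with one reading. The BMI criterion also implies some screening weight, although its source is not given and it is not the outcome measure.

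Two further points stand. A bias toward zero cannot by itself create a false superiority claim. And because weights upload automatically every day, a pre-diet baseline may be recoverable from data already held. The second point is a reason to make the correction now.

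**Conclusion.** The point holds as a defect in a stated rule for the primary endpoint. Baseline body mass is defined inconsistently and is not anchored before the diet. Followed literally, the rule can make the first diet week the baseline.

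The size depends on the reading. It is zero if baseline is a pre-diet weigh-in. It is 4 to 23% of the 5 kg target (change score) or 3 to 17% (baseline-adjusted) if baseline is the mean of diet week 1 and the Keyto arm loses 0.5 to 2 kg more than the Weight Watchers arm by day 7. That range, the linear course within the week and the slope of 0.75 for the adjusted analysis are assumptions, and only the 5 kg, 15 kg and r = 0.75 come from the article. The direction toward zero also assumes that the Keyto arm loses more early. If the Weight Watchers arm did, the sign would reverse. The rule should be settled before the 12-week analysis.

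**What to change.** Amend the Body Mass section so that baseline, in both arms, is the weigh-in or weigh-ins time-stamped on or before the morning on which the participant starts the diet. Keep the weekly mean for weeks 12, 24 and 48 only. Apply one rule to all participants, including the 49 enrolled as of April 2020, whose baseline can be re-derived from the uploaded readings where the dates allow. State in the same place how a randomised participant with no qualifying reading enters the intention-to-treat analysis.

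The cost is a short amendment and a re-derivation from existing data. The downside is that a baseline resting on few readings is slightly noisier than a 7-day mean.

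Sending the scale before randomisation to the remaining 144 − 49 = 95 participants, so that each has a weight before allocation, is an optional addition. It changes enrolment logistics mid-trial and is not needed for the fix.

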##### Venous Blood Sample

Participants will be sent to a third-party blood clinic (Quest Diagnostics), to provide a ≥12 hour fasting blood sample obtained by venipuncture from an antecubital vein in the seated position. Blood samples will be obtained at baseline and 12 weeks, with an optional blood sample obtained at 48 weeks. See Table 1 for a complete of list of blood measures including hemoglobin A_1_c, blood glucose, insulin sensitivity, and fasting lipids.

##### 24-Hour Dietary Recall

Participants will complete the Automated Self-Administered 24-Hour Dietary Recall [26] to determine caloric intake and macronutrient composition. Participants will be asked to report all caloric intake within the past 24 hours at baseline and at 12, 24, and 48 weeks. This retrospective questionnaire allows for extraction of detailed information regarding specific nutrients and food groups (eg, carbohydrate intake, consumption of saturated fat). The Automated Self-Administered 24-Hour Dietary Recall has demonstrated high consistency with interviewer assessed 24-hour diet (*r*=0.80) [27] and with 4-day food records [28].

##### Sleep Quality

The Pittsburgh Sleep Quality Index [29] is a validated measure used to assess sleep schedules and sleep quality. The questionnaire assesses quality of sleep from the previous month by measuring the following components: subjective sleep quality, sleep latency, sleep duration, habitual sleep efficiency, sleep disturbances, use of sleep medication, and daytime dysfunction. An overall score will be calculated by totaling these component scores whereby lower scores denote a higher sleep quality. Sleep quality will be assessed at baseline and at 12, 24, and 48 weeks.

#### Demographics

Participant characteristics, including sex, race or ethnicity, education level, occupation, income, marital status, and number of dependents will be collected at baseline via online survey.

#### Manipulation Checks

##### App Data

We will extract app usage data, food logs, breath acetone levels (for the Keyto group only), and weight.

##### Food Attitudes Survey

Participants will complete the Food Attitudes Survey [30], a short, 9-item survey to assess their thoughts and feelings toward food. Participants will be asked, “On a 5-point scale, answer how these comments reflect your thoughts and feelings toward food,” where scores range from 1 (not at all like me) to 5 (exactly like me). An example stem item reads, “It is difficult for me to leave food on my plate.” Attitudes will be measured at baseline and at 12, 24, and 48 weeks.

##### Cravings, Mood, And Energy

This 12-item questionnaire asks participants about the impact of their dietary intervention on aspects of their cravings, mood, and energy in order to determine possible barriers to diet adherence. Participants will be asked, “How does the following impact your ability to stick with your diet?” An example craving response includes, “Having delicious foods in front of you and you can’t resist.” An example mood response includes, “Having a really hard or stressful day.” An example of an energy response includes, “You become too hungry and can’t continue to resist eating.” Responses are rated on a 4-point scale ranging from 1 (not at all) to 4 (every day). As these are manipulation checks and to not overburden participants, 3 of the 12 items will be randomly asked per week. By the primary endpoint at 12 weeks, each participant will have answered each of the 12 questions 3 times. This measure was developed for this study in consultation with a health psychologist and registered dietician.

##### Diet Adherence

Diet adherence will be assessed using 2 questions relating to adherence with the diet participants were randomized to. Participants will be asked, “To what extent do you believe you were able to stick to the diet as part of this study in the past week?” on a 5-point scale ranging from 0 (not at all) to 4 (completely). There will be an open-ended response option for participants to provide an explanation if they wish. Second, participants will be asked, “How often did you monitor and track your food intake on average each day in the past week?” on a 4-point scale ranging from 0 times per day to 3 or more times per day. Participants will be asked about their diet adherence at the end of every week throughout the 48-week trial period.

##### Physical Activity

The Godin Leisure-Time Exercise Questionnaire [31] is a validated and commonly used self-report measure of physical activity. Participants will be asked to report the number of 30-minute bouts of light, moderate, and vigorous physical activity they engaged in over the past week. The Godin Leisure-Time Exercise Questionnaire will be assessed at 12 and 48 weeks.

### Sample Size Calculation

There are no known studies with protocol design as we describe. Thus, the amount of weight loss expected with a hands-off self-monitoring ketogenic mHealth application is not known. Thus, we determined sample size in order to detect a clinically meaningful 5% difference in weight loss, assuming a mean body mass of 100 kg with a standard deviation of 15 kg [32]. A 5% weight loss corresponds to a small-to-moderate effect size (Cohen *d*=0.33, *f*=0.165). Using G*Power software (version 3.1.9.3) a total sample size of 124 is required to detect a between groups effect with 80% power and α=.05 with 2 groups and 2 time points (primary outcome at 12 weeks) assuming a correlation among repeated measures of *r*=0.75. In order to preserve power and account for 15% loss to follow-up, we will aim to recruit 144 participants (ie, n=72 per group).

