### Planned Analysis

A statistician independent of the research team will analyze the data. Data will be analyzed on an intention-to-treat basis. Descriptive statistics (mean, SD, and frequency) will be calculated. Univariate and multivariate statistical assumptions will be examined and managed according to recommendations by Tabachnick and Fidell [33]. Mixed linear effects models will be used to assess between-group differences across time. All primary and secondary study outcomes will be analyzed similarly. Follow-up mean comparisons and Cohen *d* effect sizes will used to examine differences between individual time study points. Two rounds of analyses will occur: the primary outcome (body mass) and key secondary outcomes (blood variables, surveys, app data) will be assessed at the 12 weeks and follow-up exploratory analyses will be performed after 24 and 48 weeks. An additional exploratory mixed effects model using all daily body mass measures during the first 12 weeks will examine whether the patterns of body mass change differ between the 2 study groups.

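### The sample size of 124 does not follow from the test that the protocol describes; whether power is near 80% depends on how baseline enters the primary model

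*Protocol article*

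**What the plan says.** The Sample Size Calculation section sets out to "detect a clinically meaningful 5% difference in weight loss, assuming a mean body mass of 100 kg with a standard deviation of 15 kg". It turns this into a standardised effect ("A 5% weight loss corresponds to a small-to-moderate effect size", d=0.33, f=0.165) and reports that in G*Power "a total sample size of 124 is required to detect a between groups effect with 80% power", with α=.05, 2 groups, 2 time points and a correlation of 0.75 among repeated measures. It then inflates the figure: "In order to preserve power and account for 15% loss to follow-up, we will aim to recruit 144 participants", 72 per group.

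The Planned Analysis section says "Mixed linear effects models will be used to assess between-group differences across time". It does not say whether baseline body mass is an outcome in the model, a covariate, or constrained equal between arms. Table 1 gives the primary outcome as change in body mass at 12 weeks.

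**The concern.** The section names the software, the effect tested and every input, so the result can be checked, and it fails the check. A repeated-measures between-groups effect takes the arm difference averaged over the time points. A correlation of 0.75 makes that test less efficient, because the second measurement adds little new information. It is also not the contrast that answers the hypothesis, which concerns the arms' difference in weight loss at week 12.

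At stake is the justification for the trial's size. The 80% figure is attached to a test that has about 50% power at 124. The contrasts that do address the hypothesis have different power from each other, and a reader cannot tell which one the number was meant for.

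**Working it through.** **Inputs, all from Sample Size Calculation:** difference 5 kg (5% of 100 kg), SD of body mass 15 kg, r=0.75, α=.05, power 80%, 2 equal groups, 2 time points, 15% loss. Sidedness is not stated; two-sided is assumed. The effect size is d=5/15=0.333, so f=0.1667; the article rounds to d=0.33 and f=0.165. Both values of f are used below.

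**1. The test as described (repeated measures, between factors).** The noncentrality is λ = f²·N·m/[1+(m−1)r] with m=2, that is f²·N·2/1.75, referred to F(1, N−2).
- f=0.165: N=256; power at 124 is 49.6%.
- f=1/6: N=250; power at 124 is 50.3%.

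**2. The same f entered as a within-between interaction.** λ = f²·N·m/(1−r) = f²·N·2/0.25.
- f=0.165: N=40. f=1/6: N=38.
- This is too small for the stated target. A 5 kg difference present only at week 12 moves each of the four cell means by 1.25 kg from additivity, so the interaction f is 1.25/15=0.083, half of the f entered.

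Neither route gives 124. One-sided testing does not rescue it: the between-groups test then needs 198 to 202.

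**3. Arm-by-time contrast, baseline unconstrained (difference in change).** SD of change = 15·√[2(1−0.75)] = 10.61 kg; 5/10.61 = 0.471.
- F test: N=144 (148 with f=0.165). Normal approximation: 142.

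**4. Baseline-adjusted difference at week 12.** Residual SD = 15·√(1−0.75²) = 9.92 kg; 5/9.92 = 0.504.
- Normal approximation: n per arm = 2·(1.960+0.842)²·9.92²/5² = 61.8, rounded up to 62, total **124**, power 80.1%. This reproduces the article's figure.
- F test: N=126 (130 with f=0.165).

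**5. Another possible origin of 124.** For the effect averaged over two time points, SD = 15·√(1.75/2) = 14.03 kg. The normal approximation gives 2·(1.960+0.842)²·14.03²/5² = 123.6, so 124 *per arm* and 248 in total. A per-group number read as a total would also print as 124.

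**6. Dropout.** 124/0.85 = 145.9, so 146. Recruiting 144 leaves 144×0.85 = 122.4, so 122.

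| Test (two-sided, F) | Total N for 80% | Power at 124 | Power at 122 |
|---|---|---|---|
| Between-groups effect as described | 250–256 | 50% | 49–50% |
| Arm-by-time (change) | 144–148 | 73–74% | 72–73% |
| Baseline-adjusted week 12 | 126–130 | 79–80% | 78–79% |

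The first figure for N in each row uses f=1/6, the second f=0.165.

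**The case against.** The best defence is that the number is sound and only its label is loose. The phrase about a between-groups effect can be read as shorthand for a difference between arms. A baseline-adjusted comparison on the same three inputs gives exactly 124 by normal approximation. The article is condensed, and how baseline enters the mixed model is ordinarily settled in an analysis plan that is not shown. The correlation of 0.75 is itself an assumption: at 122 completers the change contrast passes 80% at r=0.79, and falls to 66% at r=0.70.

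Much of this stands. A reader might infer from the 250 to 256 that the trial is half the size it needs to be, or that 80% power is simply not delivered. The document does not support either reading. The primary outcome is weight change at 12 weeks, and nowhere is an effect averaged over baseline and week 12 named as the primary comparison. The 250 to 256 shows that the description is wrong; it is not a recruitment target. Leaving the handling of baseline to an analysis plan is likewise no fault.

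What does not stand is that the text is therefore acceptable. It attributes 124 to G*Power with repeated-measures inputs, not to an analysis of covariance or a normal approximation. With the printed f=0.165, the F-based baseline-adjusted figure is 130. A per-group number mistaken for a total remains possible. This is a stated calculation that does not yield its stated result, not a detail left for later.

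**Conclusion.** The point holds as an error in the stated calculation: 124 does not follow from the test and inputs given. It does not hold as a claim that the trial is badly underpowered. On the plan's own 5 kg, SD 15 kg and r=0.75, two-sided, with 122 completers, power is about 79% if the primary contrast adjusts for baseline and about 73% if it is an unconstrained arm-by-time contrast. The first is essentially what was intended; the second is a modest shortfall, and would reach 80% only with about 144 analysable participants, that is, with no loss. The choice of model is therefore worth about six points of power.

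The inflation slip is minor: 146 against 144 is two participants and less than one percentage point of power (79.5% at 124, 78.8% at 122, baseline-adjusted with f=1/6).

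**What to change.** - State which test produced 124, and remove the description of it as a between-groups effect over two time points.
- Name the primary contrast as the baseline-adjusted arm difference in week-12 body mass, by ANCOVA or by a mixed model with the arms' baseline means constrained equal. The constrained mixed model fits within the analysis already planned.
- Restate the calculation: 5 kg, SD 15 kg and r=0.75, two-sided α=.05, require about 126 analysable participants; 144 recruited with 15% loss leaves 122 and about 79% power.
- If an unconstrained arm-by-time test is kept instead, state its power as about 73%.
- Inflate by dividing by 0.85, or say plainly that 144 leaves 122.

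The cost is wording in the protocol and analysis plan. Recruitment stays at 144, no participants are added, and the stated power moves from 80% to about 79%. Fixing baseline adjustment in advance secures the higher of the two power figures.

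### Recruiting 144 covers about 13.9% loss to follow-up, not the stated 15%: a minor shortfall of 2 participants against the required 124

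*Protocol article*

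**What the plan says.** The Sample Size Calculation section of the protocol article states that "a total sample size of 124 is required to detect a between groups effect with 80% power", at a significance level of .05. The next sentence gives its aim as keeping that power, and sets the target: "account for 15% loss to follow-up, we will aim to recruit 144 participants", which it splits as 72 per group.

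The figure of 144 is repeated in the Methods part of the Abstract and under Participants and Eligibility. The section Recruitment, Screening, Randomization, Enrollment fixes the allocation: "All 144 participants will be randomized at 1:1 ratio to the Keyto (n=72) or Weight Watchers (n=72) trial arms".

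The article does not state the formula that takes 124 to 144, and no other section corrects or qualifies the figures.

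**The concern.** A loss allowance has one purpose: after the assumed fraction has dropped out, the number left should be at least the number the power calculation requires. All three quantities are printed here (124 required, 15% lost, 144 recruited), so a reader can check the step without any outside figure. The check fails by a small margin.

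What is at stake is the accuracy of a planning statement, not the viability of the trial. The recruitment target is a figure the trial relies on, and the sentence says it protects the planned power at a loss rate where, on the protocol's own numbers, it falls slightly short.

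**Working it through.** **Inputs** (all from Sample Size Calculation; the 1:1 split is also in Recruitment, Screening, Randomization, Enrollment)

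- Required total: 124, that is 62 per arm
- Loss to follow-up: 15%
- Recruitment target: 144, that is 72 per arm
- Power 80%, significance level .05 (sidedness is not stated; two-sided assumed here)
- Difference 5% of 100 kg = 5 kg, SD 15 kg, correlation 0.75

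**Step 1. Can the plan's own figures be reproduced?**

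- *124.* A baseline-adjusted comparison of two means has residual SD 15 x √(1 - 0.75²) = 9.92 kg. Then n per arm = 2 x (1.960 + 0.842)² x 9.92² / 5² = 61.8, so 62 per arm and 124 in total. This matches the printed figure. It does not show that this was the calculation run; the rest of the check takes 124 as given.
- *144.* Multiplying by one plus the loss rate, per arm, gives 62 x 1.15 = 71.3, rounded up to 72, so 144 in total. This matches exactly, but the article does not say that it was the method.

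**Step 2. What remains after 15% loss from 144?**

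- 144 x (1 - 0.15) = 122.4, or 61.2 per arm.
- In whole people, 15% of 144 is 21.6. Losing 21 leaves 123 and losing 22 leaves 122. Both are below 124.

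**Step 3. What target keeps 124 after 15% loss?**

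- N/(1 - d) = 124/0.85 = 145.9, so 146 (73 per arm).
- Check: 146 x 0.85 = 124.1.
- Gap to the stated target: 146 - 144 = 2 participants, or 2/146 = 1.4%.

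**Step 4. What loss does 144 cover?**

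- 1 - 124/144 = 20/144 = 13.9%.

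**Step 5. What is the cost in power?**

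- Suppose 124 gives exactly 80%. On the normal approximation the standardised difference at 124 is 1.960 + 0.842 = 2.802. At 122 it is 2.802 x √(122/124) = 2.779. Power = Φ(2.779 - 1.960) = Φ(0.819) = 79.4%.
- A two-sided t test calibrated to 80.0% at 124 also gives 79.4% at 122.
- The baseline-adjusted formula of Step 1 gives 80.1% at 62 per arm and 79.5% at 61 per arm.
- On each route the loss is about 0.6 percentage points.

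**The case against.** The strongest objection is materiality. The gap is one participant per arm. The 15% is itself a round planning guess, and the distance between 13.9% and 15% is smaller than any realistic uncertainty in that guess. A change of 0.6 points in nominal power alters no decision about design, analysis or conduct. This stands, and it is why the point is minor. It does not make the sentence right: all the inputs are exact, and rounding does not take 145.9 to 144.

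A second objection concerns the analysis set. Planned Analysis specifies intention-to-treat with mixed linear effects models, which can use participants with partial data, so those who complete follow-up are not strictly the analysis set. This also stands, and it softens the point. It does not remove it. The protocol itself adds a loss allowance to 124, and so treats lost participants as not counting towards the requirement. In a model with two time points, someone lost before week 12 supplies only a baseline weight and adds little to the 12-week comparison.

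A third objection is that the base figure of 124 matters far more. It fits a baseline-adjusted comparison. A repeated-measures between-groups test with the printed inputs (f = 0.165, 2 time points, correlation 0.75) would need about 255. That is a separate question. The present point neither depends on it nor implies that 124 is sound.

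A reader might also infer that the wrong inflation formula was used, and that the same error would carry into any revised target. The documents do not support this. The match with 62 x 1.15 is suggestive, but the formula is not given and no revision is proposed.

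**Conclusion.** The point holds as a small inconsistency in one sentence: the printed 144 does not keep the printed 124 at the printed 15% loss.

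The conclusion on head count rests on the protocol's figures alone. The conclusion on power also assumes that 124 gives 80% power, that the test is two-sided, and that participants lost before week 12 contribute essentially nothing to the primary comparison. If they contribute something through the mixed model, the cost in power is smaller still.

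A reader might go further and conclude that the trial is underpowered because of the loss allowance, or that its target is unusable. Neither follows. A deficit of 1.4% in recruits is at the level of rounding, and nothing in the interpretation of the trial would turn on it.

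**What to change.** Keep 144 and restate the sentence in Sample Size Calculation in one of two ways:

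- the target of 144 allows for up to about 13.9% (approximately 14%) loss to follow-up while retaining 124 participants; or
- with 15% loss, about 122 of the 144 participants remain, and power is just under 80% (about 79.4%).

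If the base figure of 124 is ever revised for other reasons, compute the new target as N/(1 - 0.15) and round up to equal arms.

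The cost is one corrected sentence. No extra participants are needed, and the other places that cite 144 stay as they are. The only price is that the stated loss allowance or the stated power becomes slightly less favourable.
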